### **7.5 Management and monitoring of AEs**

Dose modifications: there will be no dose modifications in this study. Patients with severe chemotherapy toxicity or patients who delay chemotherapy for more than 2 weeks due to adverse events are recommended to withdraw from the study.

Sintilimab treatment may be temporarily suspended in patients experiencing toxicity considered related to study treatment. If corticosteroids are initiated for treatment of the toxicity, the must be tapered over > 1 month to <10 mg/day or oral prednisone or equivalent before sintilimab can be resumed. If sintilimab is withheld for > 12 weeks treatment can be resumed prior approval by the principal investigator. In Table 1 is reported a guideline for the management of patients who experienced specific adverse events (see also Appendix 5).

AEs associated with sintilimab exposure may represent an immunologic etiology. These immune-related AEs (irAEs) may occur shortly after the first dose or several months after the last dose of sintilimab treatment and may affect more than one body system simultaneously. Therefore, early recognition and initiation of treatment is critical to reduce complications. Based on existing clinical study data, most irAEs were reversible and could be managed with interruptions of sintilimab, administration

of corticosteroids and/or other supportive care. For suspected irAEs, ensure adequate evaluation to confirm etiology or exclude other causes. Additional procedures or tests such as bronchoscopy, endoscopy, skin biopsy may be included as part of the evaluation. Based on the severity of irAEs, withhold or permanently discontinue sintilimab and administer corticosteroids. Dose modification and toxicity management guidelines for irAEs associated with sintilimab are provided in Table 1.

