|                              | Grade 4 or recurrent Grade 3   | Permanently discontinue                                                                                                                                  |                                                                                                             |                                                                                                                            |

1. Withhold or permanently discontinue sintilimab is at the discretion of the investigator or treating physician.

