## APPENDIX 5 - RECOMMENDED TREATMENT MODIFICATIONS FOR SINTILIMAB

| Immune-related adverse                                                                                                                             | Severity                                                                                                                                                                                 | Treatment modification                                                                                                                                                                                                                                                                                                                                                                                                        |
|----------------------------------------------------------------------------------------------------------------------------------------------------|------------------------------------------------------------------------------------------------------------------------------------------------------------------------------------------|-------------------------------------------------------------------------------------------------------------------------------------------------------------------------------------------------------------------------------------------------------------------------------------------------------------------------------------------------------------------------------------------------------------------------------|
| Pneumonitis                                                                                                                                        | Grade 2                                                                                                                                                                                  | Withhold until adverse reactions recover to Grade 0-1*                                                                                                                                                                                                                                                                                                                                                                        |

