|                                                                                                                                                    | Grade 3 or 4, or recurrent Grade 2                                                                                                                                                       | Permanently discontinue                                                                                                                                                                                                                                                                                                                                                                                                       |
| Colitis                                                                                                                                            | Grade 2 or 3                                                                                                                                                                             | Withhold until adverse reactions recover to Grade 0-1*                                                                                                                                                                                                                                                                                                                                                                        |
|                                                                                                                                                    | Grade 3 or 4, or recurrent Grade 3                                                                                                                                                       | Permanently discontinue                                                                                                                                                                                                                                                                                                                                                                                                       |

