| Note: toxicity grades are in accordance with National Cancer Institute Common Terminology Criteria for Adverse Events Version 4.0 (NCI-CTCAE v.4). |                                                                                                                                                                                          |                                                                                                                                                                                                                                                                                                                                                                                                                               |

\* If treatment-related toxicity does not resolve to Grade 0-1 within 12 weeks after last dose of KEYTRUDA, or if corticosteroid dosing cannot be reduced to  $\leq 10$  mg prednisone or equivalent per day within 12 weeks, KEYTRUDA should be permanently discontinued.

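### Recommended sintilimab modifications conflict for first Grade 3 colitis (Appendix 5 against itself and Table 1) and for recovery after week 12 (Appendix 5 footnote against section 7.5)

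*Protocol*

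**What the plan says.** Section 7.5 of the protocol refers the reader to Table 1 for managing specific adverse events and adds a bracketed pointer to Appendix 5. Its closing sentence names Table 1 alone as the place for immune-related toxicity guidance. Both tables are headed as recommendations; the appendix is titled "RECOMMENDED TREATMENT MODIFICATIONS FOR SINTILIMAB".

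**Colitis.** Table 1 (diarrhea/colitis) withholds sintilimab at Grade 2 or 3 and stops it permanently at Grade 4. In Appendix 5 the colitis row for Grades 2 and 3 reads "Withhold until adverse reactions recover to Grade 0-1". The next row, for permanent discontinuation, is triggered by "Grade 3 or 4, or recurrent Grade 3". For the residual class of other immune-related events, both tables use "Grade 4 or recurrent Grade 3" as the trigger for a permanent stop.

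**Recovery after 12 weeks.** Section 7.5 states: "If sintilimab is withheld for > 12 weeks treatment can be resumed prior approval by the principal investigator". The asterisk on the withhold rows of Appendix 5 leads to a footnote that begins "If treatment-related toxicity does not resolve to Grade 0-1 within 12 weeks after last dose of KEYTRUDA". It adds a second condition, failure to get corticosteroids to at most 10 "mg prednisone or equivalent per day within 12 weeks, KEYTRUDA should be permanently discontinued". Section 7.5 also sets a steroid condition for restarting: the dose must be "tapered over > 1 month to <10 mg/day or oral prednisone or equivalent before sintilimab can be resumed".

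**The concern.** These are the instructions an investigator uses to decide whether a patient may be re-exposed to a checkpoint inhibitor after a serious immune-related event. Where two parts of one protocol answer differently, two investigators can each comply and yet do opposite things with the same patient: one restarts, the other stops for good. That is a patient-safety problem, and it also makes treatment exposure depend on which page a site consults.

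The footnote adds a difficulty. Read literally, it governs a drug that nobody in this trial receives, so its 12-week limit would not apply to sintilimab. Read as a rule for sintilimab, which the asterisks and the appendix title suggest, it contradicts section 7.5. Either reading needs a correction.

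**Working it through.** The plan gives no figure to reproduce, and the point depends on no sample size or error rate. The check is to apply the texts to the same patient.

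**Case 1: colitis.**

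| Event | Table 1 | Appendix 5 |
|---|---|---|
| Grade 2 | withhold | withhold |
| First Grade 3 | withhold | withhold **and** permanent stop |
| Recurrent Grade 3 | withhold (no separate trigger) | withhold **and** permanent stop |
| Grade 4 | permanent stop | permanent stop |

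A first Grade 3 colitis meets both Appendix 5 rows, so the appendix contradicts itself before any comparison with Table 1. Its stop row is also redundant: if every Grade 3 ends treatment, naming recurrent Grade 3 adds nothing. Since both tables use "Grade 4 or recurrent Grade 3" for other immune-related events, the colitis row is probably a slip for that wording. The intent is an inference; the contradiction is on the page. Correcting the appendix row alone would still leave recurrent Grade 3 as a withhold in Table 1 and a stop in Appendix 5, so Table 1 needs the same wording.

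**Case 2: recovery after week 12.** Take a patient with a non-endocrine toxicity that first reaches Grade 0-1, with steroids below 10 mg/day after the required taper, at week 14 after the last dose.

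- *Appendix 5 footnote, read as a sintilimab rule:* 14 > 12, so the drug is permanently discontinued. No approval route is given.
- *Section 7.5, hold counted from the last dose:* 14 > 12, so the drug may resume with the principal investigator's approval.
- *Section 7.5, hold counted from the first missed dose:* with a 21-day (3-week) cycle, 14 − 3 = 11 weeks, which is not above 12, so the approval sentence is not reached and resumption is not barred.

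On either count section 7.5 permits what the footnote forbids. If toxicity and steroid dose had both met the footnote's conditions within 12 weeks, the footnote would not require a stop and the two texts would agree. The clash is therefore confined to late recovery or late steroid reduction.

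**When case 2 can arise.** During induction, section 7.4 (item 3) blocks a new course until immune-related events are at Grade 0 or 1, which delays pegaspargase as well. Section 7.5 then recommends leaving the study once chemotherapy is delayed for more than 2 weeks. After cycles 1 to 5 that recommendation would usually take effect long before week 12. Pegaspargase is given for 6 cycles only (section 7.1), so after the sixth dose no further chemotherapy course can be delayed. The 12-week clash therefore matters mainly from cycle 6 onward.

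**Can another part of the protocol settle it?** Section 7.5 favours Table 1 but has no clause saying that it prevails. Table 1 has no 12-week rule, so giving it precedence would resolve case 1 but not case 2.

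**The case against.** The strongest reply is that the protocol's intent is clear enough. Section 7.5 names Table 1 twice and the appendix once, in brackets; Table 1 is unambiguous on first Grade 3 colitis; both tables are recommendations and the footnote says only what should be done. On the 12-week point, a literal reader may say that the footnote does not bind sintilimab, leaving section 7.5 as the only rule. That rule has safeguards: a taper over more than a month, approval, and the section 7.4 requirement of Grade 0 or 1 before a new cycle.

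Much of this stands. The colitis conflict is mainly an error in the appendix, and the texts are guidance. But opposite recommendations for one patient are not usable guidance, and repeated mention of Table 1 is not a precedence rule. The literal reading of the footnote leaves asterisks on sintilimab rows that lead to a rule for another drug.

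Some stronger readings are tempting but unsupported:

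- *The steroid thresholds contradict each other.* They do not. Below 10 mg/day is a condition for resuming; at most 10 mg/day is the condition for avoiding a permanent stop. A patient on exactly 10 mg/day at week 12 satisfies the footnote and simply tapers further before restarting.
- *Sintilimab could be restarted late without control.* The safeguards listed above rule this out.
- *The 12-week clash affects patients throughout treatment.* The delay rule largely pre-empts it in cycles 1 to 5, although only by recommendation.
- *The trial's statistical properties are damaged.* The sample-size statement in section 9.1 uses none of these rules.

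**Conclusion.** The point holds as an internal inconsistency in the safety instructions, in two places: first Grade 3 colitis, and recovery or steroid reduction later than 12 weeks. It should be fixed, because the instructions concern rechallenge with a checkpoint inhibitor and nothing in the protocol resolves them.

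Its size cannot be given as a number of patients: the protocol states no expected rate of Grade 3 colitis or of late recovery among the 22 planned. For an affected patient the difference is between restarting and permanently stopping. No effect on power or type I error follows.

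The conclusion on colitis rests on the text alone. The conclusion on late recovery assumes that the footnote was meant for sintilimab, as its asterisks and the appendix title indicate. If it was not, the defect is instead a footnote that applies to no study drug.

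**What to change.** **Colitis.** Change the Appendix 5 permanent-stop row to Grade 4 or recurrent Grade 3, and put the same trigger in the Table 1 colitis row. Both then match the wording already used for other immune-related events. Add to section 7.5 that Table 1 governs wherever the two tables differ.

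**Twelve-week rule.** Replace KEYTRUDA with sintilimab in the footnote and state one rule, on one clock, in both section 7.5 and Appendix 5. Suggested wording: *Sintilimab is stopped permanently if, 12 weeks after the last dose, toxicity remains above Grade 1 or corticosteroids remain above 10 mg/day of prednisone or equivalent. Endocrine events at Grade 2 or below that are controlled by replacement therapy or metabolic control are exempt. A patient who met both conditions in time but restarts after a hold of more than 12 weeks needs the principal investigator's approval.* The exemption preserves the note under Table 1 and the endocrine row of Appendix 5. Keep the section 7.5 threshold of below 10 mg/day for resuming.

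**Cost.** Amendment text only, with no new visits or data. The real downside is clinical: a patient who recovers after week 12 loses the chance of rechallenge by approval. If the sponsor wants to keep that chance, the footnote can be rewritten to allow it; what matters is that both places say the same thing.

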**Table 1: Recommended treatment modifications for Sintilimab**

| Immune-related AEs                               | Toxicity grade or conditions (CTCAEv4.0)                                                         | Action taken to Sintilimab                       | irAE management with corticosteroid and/or other therapies                                                                                                                                  | Monitor and follow-up                                                                                                                                                                                                                                                                                                                                                                                                                                                                                                                                                                                                                            |
|--------------------------------------------------|--------------------------------------------------------------------------------------------------|--------------------------------------------------|---------------------------------------------------------------------------------------------------------------------------------------------------------------------------------------------|--------------------------------------------------------------------------------------------------------------------------------------------------------------------------------------------------------------------------------------------------------------------------------------------------------------------------------------------------------------------------------------------------------------------------------------------------------------------------------------------------------------------------------------------------------------------------------------------------------------------------------------------------|
| Pneumonitis                                      | Grade 2                                                                                          | Withhold                                         | 
 
Administer corticosteroids (initial dose of 1-2 mg/kg prednisone or equivalent) followed by taper
 
                                         | 
 
Monitor participants for signs and symptoms of pneumonitis
 
Evaluate participants with suspected pneumonitis with radiographic imaging and initiate corticosteroid treatment
 
Add prophylactic antibiotics for opportunistic infections
 
                                                                                                                                                                                                                                                                                                                                        |
|                                                  | Grade 3 or 4, or recurrent Grade 2                                                               | Permanently discontinue                          |                                                                                                                                                                                             |                                                                                                                                                                                                                                                                                                                                                                                                                                                                                                                                                                                                                                                  |
| Diarrhea / Colitis                               | Grade 2 or 3                                                                                     | Withhold                                         | 
 
Administer corticosteroids (initial dose of 1-2 mg/kg prednisone or equivalent) followed by taper
 
                                         | 
 
Monitor participants for signs and symptoms of enterocolitis (ie, diarrhea, abdominal pain, blood or mucus in stool with or without fever) and of bowel perforation (ie, peritoneal signs and ileus).
 
Participants with <math>\geq</math> Grade 2 diarrhea suspecting colitis should consider GI consultation and performing endoscopy to rule out colitis.
 
Participants with diarrhea/colitis should be advised to drink liberal quantities of clear fluids. If sufficient oral fluid intake is not feasible, fluid and electrolytes should be substituted via IV infusion.
 
 |
|                                                  | Grade 4                                                                                          | Permanently discontinue                          |                                                                                                                                                                                             |                                                                                                                                                                                                                                                                                                                                                                                                                                                                                                                                                                                                                                                  |
| AST / ALT elevation or Increased bilirubin       | Grade 2                                                                                          | Withhold                                         | 
 
Administer corticosteroids (initial dose of 0.5- 1 mg/kg prednisone or equivalent) followed by taper
 
                                      | 
 
Monitor with liver function tests (consider weekly or more frequently until liver enzyme value returned to baseline or is stable)
 
                                                                                                                                                                                                                                                                                                                                                                                                                                                              |
|                                                  | Grade 3 or 4                                                                                     | Permanently discontinue                          | 
 
Administer corticosteroids (initial dose of 1-2 mg/kg prednisone or equivalent) followed by taper
 
                                         |                                                                                                                                                                                                                                                                                                                                                                                                                                                                                                                                                                                                                                                  |
| Type 1 diabetes mellitus (T1DM) or Hyperglycemia | Newly onset T1DM or Grade 3 or 4 hyperglycemia associated with evidence of $\beta$ -cell failure | Withhold                                         | 
 
Initiate insulin replacement therapy for participants with T1DM
 
Administer anti-hyperglycemic in participants with hyperglycemia
 
 | 
 
Monitor participants for hyperglycemia or other signs and symptoms of diabetes.
 
                                                                                                                                                                                                                                                                                                                                                                                                                                                                                                                |
| Hypophysitis                                     | Grade 2                                                                                          | Withhold                                         | 
 
Administer corticosteroids and initiate hormonal replacements as clinically indicated.
 
                                                    | 
 
Monitor for signs and symptoms of hypophysitis (including hypopituitarism and adrenal insufficiency)
 
                                                                                                                                                                                                                                                                                                                                                                                                                                                                                           |
|                                                  | Grade 3 or 4                                                                                     | Withhold or permanently discontinue  |                                                                                                                                                                                             |                                                                                                                                                                                                                                                                                                                                                                                                                                                                                                                                                                                                                                                  |
| Hyperthyroidism                                  | Grade 2                                                                                          | Continue                                         | 
 
Treat with non-selective beta-blockers (eg, propranolol) or thionamides as appropriate
 
                                                    | 
 
Monitor for signs and symptoms of thyroid disorders.
 
                                                                                                                                                                                                                                                                                                                                                                                                                                                                                                                                           |
|                                                  | Grade 3 or 4                                                                                     | Withhold or permanently discontinue  |                                                                                                                                                                                             |                                                                                                                                                                                                                                                                                                                                                                                                                                                                                                                                                                                                                                                  |
| Hypothyroidism                                   | Grade 2-4                                                                                        | Continue                                         | 
 
Initiate thyroid replacement hormones (eg, levothyroxine or liothyronine) per standard of care
 
                                            | 
 
Monitor for signs and symptoms of thyroid disorders.
 
                                                                                                                                                                                                                                                                                                                                                                                                                                                                                                                                           |
| Nephritis and Renal dysfunction                  | Grade 2                                                                                          | Withhold                                         | 
 
Administer corticosteroids (prednisone 1-2 mg/kg or equivalent) followed by taper.
 
                                                        | 
 
Monitor changes of renal function
 
                                                                                                                                                                                                                                                                                                                                                                                                                                                                                                                                                              |
|                                                  | Grade 3 or 4                                                                                     | Permanently discontinue                          |                                                                                                                                                                                             |                                                                                                                                                                                                                                                                                                                                                                                                                                                                                                                                                                                                                                                  |

|                              |                                |                                                                                                                                                          |                                                                                                             |                                                                                                                            |
|------------------------------|--------------------------------|----------------------------------------------------------------------------------------------------------------------------------------------------------|-------------------------------------------------------------------------------------------------------------|----------------------------------------------------------------------------------------------------------------------------|
| Myocarditis                  | Grade 1 or 2                   | Withhold                                                                                                                                                 | 

Based on severity of AE administer corticosteroids

          | 

Ensure adequate evaluation to confirm etiology and/or exclude other causes

 |
|                              | Grade 3 or 4                   | Permanently discontinue                                                                                                                                  |                                                                                                             |                                                                                                                            |
| All other immune-related AEs | Intolerable/persistent Grade 2 | Withhold                                                                                                                                                 | 

Based on type and severity of AE administer corticosteroids

 | 

Ensure adequate evaluation to confirm etiology and/or exclude other causes

 |
|                              | Grade 3                        | Withhold or discontinue based on the type of event. Events that require discontinuation include and not limited to: Gullain-Barre Syndrome, encephalitis |                                                                                                             |                                                                                                                            |
|                              | Grade 4 or recurrent Grade 3   | Permanently discontinue                                                                                                                                  |                                                                                                             |                                                                                                                            |

1. Withhold or permanently discontinue sintilimab is at the discretion of the investigator or treating physician.

